### 3.3 Sample size

A sample size of 30 in each group will have 80% power to detect a probability of at least 0.71 that an observation in Group 1 is less with respect to the primary outcome variable than an observation in Group 2 using a Wilcoxon (Mann-Whitney) rank-sum test with a 0.05 two-sided significance level.

Based on an expected drop-out rate of 10%, 67 participants will be recruited to participate in this study.

### 3.4 Data collection

Data will be collected from Questionnaires 1 and 2 and scoring sheets. These data will be stored in Microsoft Excel spreadsheets on a secure computer owned by the Department of Anesthesia, Intensive Care Medicine and Pain Medicine at MedUni Vienna, with access restricted to study team members. The physical files will be collected in a folder that will be stored in a locked office in an additional locked box that only study team members will have access to.

All videos will be stored on the same cloud server only in final edited and thus pseudonymized form.

#### 3.4.1 Variables

**Table 3.** Variables to be collected in this study

| Variable                                  | Data source     | Notes                                                                                                                |
|-------------------------------------------|-----------------|----------------------------------------------------------------------------------------------------------------------|
| Baseline characteristics           |                 |                                                                                                                      |
| Age                                       | Questionnaire 1 | <24; 24 – 27; 28 – 29; 30 – 32; >32 (in years)                                                                       |
| Gender                                    | Questionnaire 1 | Male/female/divers/inter/open/none                                                                                   |
| Knowledge of German                       | Questionnaire 1 | First language/fluent/basic                                                                                          |
| Experience                                | Questionnaire 1 | Junior physician (common-trunk) or first-year resident (anesthesia/intensive care; emergency medicine; traumatology) |
| Previous participation in ERC ALS courses | Questionnaire 1 | Yes/no                                                                                                               |

|                                                                                |                 |                      |
|--------------------------------------------------------------------------------|-----------------|----------------------|
| Previous participation in certified advanced trauma courses (PHTLS, ETC, ATLS) | Questionnaire 1 | Yes/no               |
| Real Life in-hospital CPR experience                                           | Questionnaire 1 | 5-point Likert scale |
| Real life out-of-hospital CPR experience                                       | Questionnaire 1 | 5-point Likert scale |
| Real life in-hospital trauma management experience                             | Questionnaire 1 | 5-point Likert scale |
| Real life out-of-hospital trauma management experience                         | Questionnaire 1 | 5-point Likert scale |
| Openness to Experience Score (HEXACO subscale)                                 | Questionnaire 1 | 1 to 5               |
| Technology Readiness Score                                                     | Questionnaire 1 | 12 to 60             |
| Experience with non-VR video games within the last 12 months                   | Questionnaire 1 | 5-point Likert scale |
| Experience with VR video games within the last 12 months                       | Questionnaire 1 | 5-point Likert scale |
| Experience with non-VR video games at the age of 6 to 18 years                 | Questionnaire 1 | 5-point Likert scale |
| Experience with VR video games at the age of 6 to 18 years                     | Questionnaire 1 | 5-point Likert scale |
| Desire for more digital tools in medical education                             | Questionnaire 1 | 5-point Likert scale |
| Primary outcome                                                         |                 |                      |
| Time to critical action #3                                                     | Scoring sheet   | Minutes : seconds    |
| Secondary outcomes                                                      |                 |                      |
| Recognition and treatment of the underlying condition                          | Scoring sheet   | Yes/no               |
| Patient declared dead prematurely                                              | Scoring sheet   | Yes/no               |
| Times to critical actions #1 and #2                                            | Scoring sheet   | Minutes : seconds    |
| Protocol deviations                                                            | Scoring sheet   | Yes/no               |
| NASA-TLX (global and per objective)                                            | Questionnaire 2 | 0 to 100 points      |
| Eye-Tracking                                                                   | Scoring sheet   |                      |
| - Dwell time in AOs                                                            |                 | Minutes : seconds    |
| - Fixation count                                                               |                 | Count                |
| - Average fixation duration                                                    |                 | Minutes : seconds    |
| - Relative time without AOI                                                    |                 | Minutes : seconds    |
| Learning method (participants' impression)                                     |                 |                      |
| - Learning progress                                                            |                 |                      |

|                                                           |                  |                      |
|-----------------------------------------------------------|------------------|----------------------|
| - Level of frustration                                    | Questionnaire 2  | 5-point Likert scale |
| - Level of enjoyment                                      |                  |                      |
| Participants' confidence in management of TCA             | Questionnaires 2 | 5-point Likert scale |
| Participants' performance                                 |                  |                      |
| - Participants' subjective impression                     | Questionnaires 2 | 5-point Likert scale |
| - Experts' impression                                     | Scoring sheet    | 5-point Likert scale |
| VR-related adverse events                                 | Questionnaire 2  | Incidence rate       |
| SUS                                                       | Questionnaire 2  |                      |
| - SUS score                                               |                  | 1 to 100             |
| - Adjective rating scale                                  |                  | 7-point Likert scale |
| Drop-out variables                                 |                  |                      |
| Training/studying with other non-study learning resources | Questionnaire 2  | Yes/no               |
| Insufficient preparation with assigned learning method    |                  | Yes/no               |

---

*ALS = advanced life support; AOI = area of interest; ATLS = advanced trauma life support; CPR = cardiopulmonary resuscitation; ERC = European Resuscitation Council; ETC = European Trauma Course; NASA-TLX = National Aeronautics and Space Administration Task Load Index; PHTLS = prehospital trauma life support; SUS = system usability scale; TCA = traumatic cardiac arrest; VR = virtual reality*

### 3.4.2 Data protection

All data collected on study participants will be pseudonymized with a sequential numerical code. Direct references to the identity of these individuals will only be found on the informed consent forms (see Section 4.1) and an Excel sheet with contact information accessible only by study team management.

All videos will be deleted three months after the completion of the study.

Only the study team has access to the data and videos collected. The data is pseudonymized, password-protected, and firewalled. In addition, the data is stored separately from the individual informed consent forms and the Excel spreadsheet containing all contact information for participants. The informed consent forms and the latter Excel spreadsheet are kept secure and only the study management has access to them. Access to the data that directly identifies participants is therefore only available to the study management. In addition, authorized representatives of the study management, who are bound to secrecy, as well as representatives of national and/or international health authorities and ethics committees may have access to these data, as far as this is necessary or required to verify the proper conduct of the study.

All persons who have access to this data are subject to the applicable national data protection regulations and/or the European Union (EU) General Data Protection Regulation (GDPR) when handling the data. The code that allows the pseudonymized data to be associated with you is kept only at the study center.

The data will only be passed on in the pseudonymized or anonymized form. The data will only be used in fully anonymized form for any publications.

According to the GDPR, participants generally have the right of access, rectification, deletion, restriction of processing, data portability and objection, if this does not make the study's objectives impossible or seriously impair them and provided that this does not conflict with other legal provisions.

### 3.4.3 Data analysis

After data collection and compilation are completed in Microsoft Excel, they will be processed for further statistical analysis. Furthermore, two independent study team members will check the data for plausibility.

## 3.5 Statistical methods

Continuous data will be reported using median and interquartile range (IQR) if skewed or mean  $\pm$  standard deviation (SD) if normally distributed. Counts and percentages with 95% confidence intervals (CI) will be given for categorical data.

### **Primary objective/outcome:**

A two-sided generalized Wilcoxon test with a 5% significance level will be used to compare the primary outcome between the randomized groups. Participants who do not identify and treat the underlying condition of TCA will be censored at 15 minutes. Furthermore, if patients are declared dead prematurely, the observation will also be censored at 15 minutes.

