### 2.3 Secondary Objectives

- 1) Comparing the number of participants who did not recognize and treat the underlying condition (one or more missed critical actions) of the TCA between randomized groups.
- 2) Comparing the number of participants who prematurely declared a patient dead (before the 15-minute time limit of the scenario).
- 3) Comparing the time to critical actions, excluding the primary outcome measure, between randomized groups.
- 4) Comparing the proportions of the respective protocol deviations between randomized groups.
- 5) Evaluate gender differences in the primary outcome.
- 6) Comparison of cognitive load between the randomized groups while performing the simulated assessment scenarios as measured by the National Aeronautics and Space Administration Task Load Index (NASA TLX).
- 7) Eye-tracking
  - a) Comparing the gaze behavior (dwell-time in AOIs, fixation count, and average fixation duration) between randomized groups.
  - b) Comparing the relative time when no AOI is illustrated between randomized groups.
- 8) Using a 5-point Likert scale:
  - a) Participants' subjective impressions of their learning progress when using VR/e-learning.

- b) Participants' subjective impressions of their level of frustration when using VR/e-learning.
  - c) Participants' subjective impression of their level of enjoyment when using VR/e-learning.
  - d) Participants' subjective confidence in recognizing and providing initial care to polytraumatized patients in cardiac arrest in the simulation sessions.
  - e) Participants' subjective overall performance in the simulation sessions.
  - f) Participants' overall performance in the simulation sessions from the expert's point of view.
- 9) To assess the correlation between how often participants have played VR and non-VR video games in the past 12 months and between the ages of 6 and 18 and the primary outcome?
- 10) The incidence rate of VR-related adverse events (AEs).
- 11) System usability scale (SUS) for the use of the VR simulations.

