### 3.2.1 Randomization

Recruited participants will be randomly assigned to the control or intervention group on an equal basis by gender. Participants will not know their allocation to either group until they have watched the entire introductory video and completed Questionnaire 1. Randomization will be performed using the web-based randomization software Randomizer from MedUni Vienna (38).

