### **Secondary objectives/outcomes:**

A two-sided generalized Wilcoxon test will also be used to compare times to critical actions, excluding the primary outcome. The number of participants who did not recognize and treat the underlying condition of the TCA, and the number of participants declaring the patient dead prematurely, will be compared between groups calculating the chi-square test. Protocol deviations will be analyzed separately for each protocol deviation listed in Table 2. The respective frequencies of each protocol deviation will also be compared between groups calculating the chi-square test. Fisher's exact test will be used if one or more expected cell frequencies are less than 5.

In addition, the Wilcoxon rank sum test will also be used to compare the gaze behavior (dwell-time in AOIs, fixation count and average fixation duration, and relative time when no AOI is illustrated) and the NASA-TLX scores (global and per objective) between randomized groups.

Furthermore, a multivariable Cox regression model (including an interaction term) will be used to determine the influence of gender on the primary outcome, and the potential modifying effect of gender on the training effect (= group effect). The HEXACO subscale and the Technology Readiness Score will also be included in the multivariable model to adjust for potential imbalances between the randomized groups.

The following Spearman correlation coefficients will be calculated corresponding to the remaining secondary objectives:

- Correlation of 5-point Likert scales between the frequency of playing classic video games and the primary outcome

5-point Likert scales, the incidence rate of VR-related AEs, and the SUS scores will be reported using descriptive statistics only.

Observations with missing data in the primary outcome measure will be excluded from statistical analyses. Boxplots will be used to illustrate calculations. A two-sided p-value of  $< 0,05$  will be considered statistically significant.

Due to the singular primary objective, no correction for multiple testing will be made. All secondary objectives are exploratory in nature and will be used to generate further hypotheses.

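### Allocation is balanced by gender but the primary test is not stratified by it; the test stays valid, yet is conservative and less efficient than a stratified one if gender is prognostic

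*Protocol*

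**What the plan says.** Section 3.2.1 of the protocol states: "Recruited participants will be randomly assigned to the control or intervention group on an equal basis by gender". It does not use the word stratified, but 1:1 allocation within gender is its natural reading, and gender is the only allocation factor named.

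The primary analysis in section 3.5 reads: "A two-sided generalized Wilcoxon test with a 5% significance level will be used to compare the primary outcome between the randomized groups". No stratum or covariate is attached. On censoring, the same paragraph adds: "Participants who do not identify and treat the underlying condition of TCA will be censored at 15 minutes".

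The sample size in section 3.3 rests on an unstratified test: "A sample size of 30 in each group will have 80% power to detect a probability of at least 0.71", "using a Wilcoxon (Mann-Whitney) rank-sum test with a 0.05 two-sided significance level".

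Gender has its own secondary objective in section 2.3 ("Evaluate gender differences in the primary outcome"). Its only place in the analysis is under the secondary outcomes of section 3.5, where "a multivariable Cox regression model (including an interaction term) will be used to determine the influence of gender on the primary outcome". That section describes all secondary objectives as exploratory.

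**The concern.** The confirmatory test leaves out the one factor that the allocation controls. When arms are balanced on a prognostic factor, that factor contributes nothing to chance differences between the arms. An unstratified test still counts the between-gender spread as noise, so it overstates the variability of the arm comparison. The result is an actual type I error below the nominal 5% and some loss of power against a test that compares the arms within gender.

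This happens only if gender is related to time to mini-thoracotomy. The protocol regards that as worth examining, since it balances on gender, sets an objective on it and plans a model with an interaction term. It does not say that an effect exists or how large one would be. What is at stake is efficiency in a trial planned for 60 evaluable participants, not a risk of false-positive findings.

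**Working it through.** **Inputs from the protocol.** 30 per group, 80% power, probability 0.71, two-sided 0.05, rank-sum test, 10% drop-out and 67 recruited (3.3); balance by gender (3.2.1); censoring at 15 minutes (3.5).

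**Assumed, because the protocol does not give them.** Gender shift b of 0, 0.5, 0.8, 1.0 or 1.5 SD of the within-gender times; normally distributed latent times; exact balance within gender; 50% women (30% as a variant); no censoring (20% as a variant).

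**1. The plan's own figure.** Noether's formula gives N = (1.960 + 0.842)² / (12 × 0.25 × (0.71 − 0.5)²) = 59.3, hence 30 per group. Power at 60 by the same formula is 80.4%. For drop-out, 60 / 0.9 = 66.7, hence 67. Both stated numbers reproduce.

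**2. Actual alpha of the unstratified test.** As a hand check with normal theory, at 50% women the gender share of the total variance is f = (b²/4) / (1 + b²/4). Balance removes this share from the arm difference, so the test statistic has SD √(1 − f) in place of 1, and alpha = 2 × [1 − Φ(1.96 / √(1 − f))].

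| b (SD) | f | 1.96/√(1 − f) | alpha by formula | alpha simulated (100,000 runs) |
|---|---|---|---|---|
| 0 | 0 | 1.960 | 5.0% | 4.9% |
| 0.5 | 0.059 | 2.020 | 4.3% | 4.3% |
| 0.8 | 0.138 | 2.111 | 3.5% | 3.4% |
| 1.0 | 0.200 | 2.191 | 2.8% | 2.8% |
| 1.5 | 0.360 | 2.450 | 1.4% | 1.3% |

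A separate simulation with 8,000 runs per setting gave 4.6%, 3.5% and 2.7% at 0.5, 0.8 and 1.0 SD. The gender-stratified rank test (van Elteren) stayed at about 5% throughout.

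**3. Power if 0.71 holds within each gender.** The arm shift is √2 × Φ⁻¹(0.71) = 0.783 SD. Simulated power, 50% women, no censoring:

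| b (SD) | Unstratified | Stratified | Loss (points) |
|---|---|---|---|
| 0 | 82.9% | 82.5% | none; stratifying costs 0.4 |
| 0.5 | 81.4% | 82.4% | 1 |
| 0.8 | 78.3% | 82.5% | 4 |
| 1.0 | 75.0% | 82.2% | 7 |
| 1.5 | 65.2% | 82.5% | 17 |

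With 30% women the loss is about 3 points at 0.8 SD and 5 at 1.0 SD. With 20% censored the pattern is the same (74.6% against 81.1% at 1.0 SD).

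**4. What step 3 implies for the overall probability.** At 50% women, two participants from opposite arms have the same gender half the time. The overall probability is therefore P = 0.5 Φ(s/√2) + 0.25 Φ((s + b)/√2) + 0.25 Φ((s − b)/√2). With s = 0.783 and b = 1.0 this is 0.5 × 0.710 + 0.25 × 0.896 + 0.25 × 0.439 = 0.689. At 0.5 and 0.8 SD it is 0.704 and 0.696. Step 3 therefore tests an overall effect somewhat smaller than 0.71.

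**5. Power if 0.71 is the overall probability.** Solving the formula in step 4 for s at P = 0.71 and simulating again (40,000 runs):

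| b (SD) | s (SD) | Unstratified | Stratified |
|---|---|---|---|
| 0.5 | 0.807 | 83.1% | 84.3% |
| 0.8 | 0.845 | 84.2% | 87.5% |
| 1.0 | 0.879 | 85.1% | 89.9% |
| 1.5 | 0.995 | 87.6% | 95.6% |

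The unstratified test stays above 80% in each setting. The stratified test has more power in each.

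**The case against.** The strongest reply is that the plan is coherent as it stands. An unstratified rank-sum test is powered, its censored-data counterpart is planned, and any departure from 5% is on the conservative side. Section 3.3 words 0.71 as a comparison of an observation in one group with an observation in the other, which is an overall probability; on that reading the 80% target is met for every gender shift examined. This stands. A reader might infer from the 78% and 75% in step 3 that the trial is underpowered. The documents do not support that, because those figures apply 0.71 within gender.

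A reader might also infer that the true alpha is below 5% whatever the facts, or that the protocol holds gender to be a performance factor. Neither follows. Without a gender effect alpha is about 5% and the unstratified test is marginally the stronger, and the protocol only asks whether gender matters.

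It can further be said that stratified randomization is inferred from section 3.2.1, that drop-out may disturb exact balance, and that Table 3 offers six gender options, so some strata could be very small. These are fair cautions. Balance by gender is nevertheless the natural reading, and a pooling rule deals with small categories.

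Finally, one may say that strata belong in the statistical analysis plan, which is not shown and may add them. But the protocol itself names the primary test, its sidedness and its level, so the point concerns a stated choice and not an absent detail.

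**Conclusion.** The point holds as a matter of efficiency, with minor to moderate importance. The primary test does not use the factor on which allocation is balanced. There is no inflation of the type I error, and the stated 30 per group and 67 recruited are correct for the test named.

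The direction of the effect is certain if gender is prognostic; its size is not, since the protocol gives no gender effect. Up to about 0.5 SD the consequence is negligible (alpha about 4.5%, power loss about 1 point). From 0.8 to 1.0 SD it becomes noticeable: alpha about 3.5% to 2.8%, with 4 to 7 points of power lost if 0.71 applies within gender, or about 3 to 5 points forgone if it applies overall. These figures assume normal latent times and exact balance within gender. The trade favours stratifying, because it costs less than 1 point if gender has no effect.

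**What to change.** In section 3.5, make the primary analysis a two-sided generalized Wilcoxon test stratified by the gender categories used for allocation, and report the unstratified test as a sensitivity analysis. Name those categories in section 3.2.1, so that the allocation and the analysis refer to the same strata. Add a rule, fixed before unblinding, that pools sparsely filled gender categories, because a stratum containing only one arm contributes nothing to the comparison.

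The cost is a few sentences. Standard software performs the test, and no further participants, data or changes in conduct are needed. The sample size in section 3.3 can remain as it is.
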